##### Cost effectiveness analysis

A cost-effectiveness analysis (CEA) will be performed comparing internet-based PA programs versus usual care, from a societal perspective for both breast cancer and prostate cancer. Two Markov decision models will therefore be constructed with mutually exclusive health states. The model will simulate the course of events in a breast and prostate cancer cohort, based on the PABLO data for comparing the two intervention strategies and compared to usual care. The models will first evaluate the cost-effectiveness using the time horizon of the study (12 months), and subsequently will simulate the expected costs and outcome with a lifetime horizon.

The cost-effectiveness of the internet-based PA programs versus usual care will be expressed as: [1] the effectiveness part of the equation will be based on EQ5D scores after 6 and 12 month follow-up. [2] the cost part of the equation will be expressed in the following items:

Direct costs: The intervention costs will be calculated, including health professional labour (including time spent on treatment per patient by social workers by means of the Activity Based Costing (ABC) method) [50], staff training, administration, and material costs (e.g. related to information technology). Costs of personnel involved in the interventions will be calculated by the time they are involved times the standard costs for (para)medical personnel. By means of the iMCQ, all patients will be asked to report on T1 and T2 about their use of health care services (e.g., GP, medical specialist, paramedical care etc.), prescribed medication use. Direct non-medical costs will include travel costs.

Indirect costs: This is the period over which the production loss is calculated, i.e. the time that an employer needs to replace a sick employee, will be measured by the Friction cost method. Therefore, an abbreviated version of the iMTA’s productivity costs questionnaire (iPCQ (see www.imta.nl/questionnaires)) will be administered at the same time points as the panel of questionnaires. The calculation of the average labour costs per working day will be based on the weighted average labour costs of full-time and part-time employed persons in the Netherlands. The friction costs are assumed to be 80% of wage costs [51]. Where appropriate, Dutch guidelines for costing studies will be used in applying tariffs to units of resource use [52]. As real-world implementation can differ from the research setting, various scenarios of implementation and compliance will be used for modelling, based on the method described by Retèl et al. [53].

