### Inclusion and exclusion criteria

#### Inclusion criteria

Patients with histologically confirmed primary breast or prostate cancer (stages: T1 – T4, N0 – N3 and M0), who may currently be receiving adjuvant endocrine treatment (breast and prostate cancer) or Trastuzumab (breast cancer) will be included in the study. Primary treatment should have been completed a minimum of 3 months and a maximum of 12 months prior to study entry. All patients need to provide written informed consent.

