### Randomisation

Patients will be allocated to one of the three study arms, using a minimization procedure that ensures balance of the groups in terms of tumor type (breast/prostate), hospital (NKI/Rijnstate), age (> 50, 50–60, > 60), and current endocrine treatment (yes/no). Participants will be randomised by the researcher, using a computer generated random assignment procedure (ALEA, [26]) to one of the two intervention groups (IPAS or IPAS+TS) or to the usual care control group with a 1:1:1 distribution. Neither participants nor researchers will be blinded to the randomization results.

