### Sample size calculation

With a total sample of 195 patients (65 per group), the study will have 80% power to detect an effect size of 0.5 for the primary outcome (change in weekly time spent in MVPA) with a *p* value of 0.05. An effect size of 0.5 typically represents a group difference or change over time that is perceived as being clinically relevant [33].

In total, 246 subjects will be recruited for this study, to allow for an attrition rate of approximately 20% (i.e., subjects who discontinue participation in the study entirely, including failure to complete all follow-up measures; those who discontinue participation in one of the groups but complete the follow-up assessments will be included in the analysis). We did not chose for a forced 50–50% inclusion of breast and prostate cancer survivors. Eligible patients will be included, regardless of the tumor type. Thus, at least 195 subjects will be available for the primary intention-to-treat analysis.

**Table 4 Tab4:** Outcome measures and measurement time points

Outcome	Measured by	Baseline	6 months	12 months	Continuously
PRIMARY					
Physical Activity	Objectively (Accelerometers and GPS-trackers)	x	x	x	
SECONDARY					
Physical Activity	Self-reported (IPAQ)	x	x	x	
Stage of behaviour change	Stage of change	x	x	x	
Fatigue	MFI	x	x	x	
Mood	POMS				
Quality of life	SF-36 and EQ5D	x	x	x	
OTHER OUTCOMES					
Cost outcomes	iMCQ iPCQ		x	x	
Social-demographic and clinical data	Social-demographic questions and patient medical file	x			
Moderators and Mediators of PA	Social-demographic questions and patient medical file	x			
Non-participation data	Reasons of non-participation question + Baseline questionnaire.	x			
Compliance	Questionnaire + Portal log data		x		x
Patient evaluation of the program	Questionnaire		x		
Contamination question for control group	Question on alternative PA program participation		x	x	

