#### Other outcomes

##### Socio-demographic and clinical data

The patients’ age, education, marital status, living situation, employment status, weight and height, medication and smoking status, and history of PA will be obtained via a questionnaire. Clinical information, including date of diagnosis, tumour characteristics, and treatment history (type of surgery, possible breast reconstruction, radiotherapy, chemotherapy, endocrine treatments) will be abstracted from the patients’ medical records. During the follow-up period, data on disease status (progression/recurrence), and any additional treatment will be obtained from the medical records.

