##### Cost effectiveness

The outcome of the cost-effectiveness analysis is the incremental cost-effectiveness ratio, expressed in cost / QALY, represents the additional costs required for the particular intervention to generate one additional QALY in comparison to doing nothing. These are calculated as follows:

ICER = (Costs of the intervention group – costs of the UC group) /

(QALYs of the intervention group – QALYs of the UC group)

Secondly, the ICER will be expressed in cost/MET minutes MVPA/week, representing the additional costs required for the gain in PA level/week.

State of the art health economic methods will be applied. These include the estimation of the degree of uncertainty about each input parameter and the use of probabilistic sensitivity analyses. Parameter values will be drawn randomly from the assigned distributions, using Monte Carlo simulation with 10,000 iterations. The degree of uncertainty will be illustrated by using confidence intervals for costs and health effects. Scatter-plots, confidence ellipses on cost-effectiveness planes and cost-effectiveness acceptability curves will be presented [57]. As an indication of whether an intervention will be considered cost-effective the ICER is compared to a range of ceiling ratios varying from €20 k / QALY for prevention to €80 k / QALY for severe diseases, in the Netherlands. If necessary, Value of Information (VOI) analysis will be performed to support decision-making regarding adoption and further research [58].

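### The cost comparison neither balances nor sets apart trastuzumab courses under way at entry, which can add avoidable chance noise to the incremental cost in the breast cancer model

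*Protocol article*

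**What the plan says.** All references are to the protocol article.

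- **Inclusion criteria.** Eligible patients are those "who may currently be receiving adjuvant endocrine treatment (breast and prostate cancer) or Trastuzumab (breast cancer) will be included in the study".
- **Randomisation.** Minimisation uses tumour type, hospital, age, "and current endocrine treatment (yes/no"). Of the two ongoing treatments named in the inclusion criteria, one is balanced and the other is not.
- **Cost effectiveness analysis (direct costs).** Under this heading, "all patients will be asked to report on T1 and T2 about their use of health care services"; the sentence goes on to prescribed medication. Cancer treatment already running at entry is not separated. The same section plans two Markov models, one per tumour type, first over 12 months and then over a lifetime.
- **Secondary outcomes and Table 4.** Cost questionnaires are completed at 6 and 12 months only, so there is no baseline cost.
- **Statistical analysis, Cost effectiveness.** The ICER numerator is "Costs of the intervention group – costs of the UC group". Uncertainty is handled by probabilistic sensitivity analysis with 10,000 iterations, confidence ellipses and acceptability curves. The ICER is judged against EUR 20,000 to 80,000 per QALY.
- **Socio-demographic and clinical data.** Medication is asked about by questionnaire. The records supply clinical information that includes "treatment history (type of surgery, possible breast reconstruction, radiotherapy, chemotherapy, endocrine treatments").

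**The concern.** A patient who enters during a trastuzumab course will probably incur costs in follow-up that a physical activity program has little means of changing. If those costs are counted by arm, any chance difference in the number of users passes into the incremental cost. The programs are described as cheap, so the real cost difference is expected to be small and even moderate noise may be large beside it. The breast cancer model uses only part of each arm, which enlarges the effect. Carrying over the covariates stated for the primary outcome (baseline MVPA and the stratification factors) would not help, because trastuzumab is not among them.

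At stake is the precision of the incremental cost, and so of the ICER, in a secondary aim that also appears in the trial's title. The primary outcome is not affected.

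**Working it through.** **1. The plan's own figure.** The article gives no figure for the cost analysis, but its sample size sets the patients per arm: "With a total sample of 195 patients (65 per group), the study will have 80% power to detect an effect size of 0.5". At two-sided alpha 0.05 (sidedness is not stated), the normal formula gives 63 per arm and the t-test 64; power at 65 per arm is about 81%. "In total, 246 subjects will be recruited for this study", "to allow for an attrition rate of approximately 20" per cent: 195 / 0.80 = 243.75, so 244 against 246. The stated figures reproduce, and 65 evaluable patients per arm is the right base.

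**2. Assumed inputs (none is in the documents).**
- Breast cancer share 50 to 80%; the article fixes no share. This gives 65 × 0.50 = 32.5 to 65 × 0.80 = 52 evaluable breast cancer patients per arm, with 65 × 0.65 = 42.25 as a middle value. Counts of whole patients use 33, 42 and 52.
- Trastuzumab users p = 5 to 20% of breast cancer patients.
- Drug cost in follow-up per user C = EUR 2,000 to 20,000.
- Program cost EUR 300 per patient.
- QALY gain 0.02.

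**3. SD of the chance cost difference between two arms:** C × √(2p(1−p)/n).
- Smallest (n = 52, p = 0.05): √(0.095/52) = 0.043, or 4.3% of C.
- Middle (n = 42.25, p = 0.10): √(0.18/42.25) = 0.0653, or 6.5% of C.
- Largest (n = 32.5, p = 0.20): √(0.32/32.5) = 0.099, or 9.9% of C.

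**4. Comparison with the program cost.** One extra user in an arm shifts its mean cost by C/n. The noise exceeds EUR 300 when the arms differ by more than 300n/C users. The probabilities treat the number of users in each arm as binomial(n, p), since minimisation does not act on trastuzumab directly. Middle case:

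| C (EUR) | SD (EUR) | Difference in users needed (n = 42) | P(noise > EUR 300) |
|---|---|---|---|
| 2,000 | 131 | 7 (from 6.3) | 2% |
| 5,000 | 326 | 3 (from 2.52) | 36% |
| 10,000 | 653 | 2 (from 1.26) | 58% |
| 20,000 | 1,305 | 1 (from 0.63) | 85% |

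Other cases, in the same order of C:
- n = 33, p = 5%: 1%, 38%, 77%, 77%.
- n = 52, p = 15%: 4%, 33%, 68%, 89%.
- n = 42, p = 5%: 0.2%, 20%, 44%, 80%.

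The 77% at EUR 10,000 with 33 per arm is on an edge. There one user is worth 10,000/33 = EUR 303, just above the threshold; with 34 per arm the probability is 39%.

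**5. On the ICER scale.** With a fixed gain of 0.02 QALY, one SD in the middle case moves the ICER by 326/0.02 ≈ EUR 16,000 per QALY at C = 5,000, and by 1,305/0.02 ≈ EUR 65,000 at C = 20,000. The largest acceptable incremental cost at EUR 20,000 per QALY would be 20,000 × 0.02 = EUR 400.

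**The case against.** The case on the other side is substantial.

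- **A reader might infer that the plan rules out adjustment.** It does not. The ICER formula is the textbook definition, an adjusted cost difference fits it equally well, and a journal article commonly leaves cost covariates to a fuller plan. This stands. What remains is that the stated minimisation factors would not cover trastuzumab.
- **A reader might infer that trastuzumab is not recorded.** The treatment-history list is introduced as examples, medication is asked about separately, and additional treatment in follow-up comes from the records. Use at entry may well be available already.
- **Whether the drug cost is captured at all is not shown.** The iMCQ is described as a generic instrument about contacts with care providers; whether it would count a hospital-given drug is unclear. Nor does the article say that trastuzumab spending enters the Markov models as an arm-specific input. The point is therefore conditional.
- **A reader might call this bias, or say that it outweighs the program.** Randomisation makes the imbalance mean-zero noise. Whether it is larger than the program cost depends on inputs that the documents do not give.
- **A reader might extend the point to breast reconstruction planned at entry.** The article lists reconstruction only under treatment history and mentions none planned at entry.
- **The planned sensitivity analysis already deals with uncertainty.** It would display this noise as wider uncertainty. It would not remove it or restore the lost precision, so this objection stands only in part.
- **Other costly events add similar noise.** True, but a treatment known at randomisation is one that can be adjusted for.

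**Conclusion.** The point holds in a limited, conditional form. If trastuzumab costs enter the arm-level costs, a pre-randomisation treatment outside the minimisation set adds avoidable noise to the incremental cost, mainly in the breast cancer model. Over the assumed ranges its SD is about 4 to 10% of the drug cost per user. Near EUR 2,000 per user this is minor. From about EUR 10,000 it exceeds an assumed EUR 300 program cost in more than half of trials when 10% or more of breast cancer patients are users. At 5% users it is somewhat below half (44% with 42 per arm). That the remaining course is settled at entry is itself an inference, since the article says only that patients may be receiving the drug. This is an optional gain in precision, not an error that threatens the trial's conclusions.

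**What to change.** Make sure that trastuzumab use at randomisation can be identified from the baseline medication question or the medical-record abstraction. State whether the cost of hospital-given trastuzumab is counted. If it is, estimate the 12-month incremental cost in the breast cancer model with a regression adjusted for use at randomisation, and report the crude difference as a sensitivity analysis.

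The cost is at most one item from records that are opened anyway, plus one covariate. The downside is that the headline incremental cost is no longer the crude difference in group costs.

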#### Amendments

Amendments are changes made to the research after a favourable opinion by the accredited Institutional Review Board (IRB) has been given. Substantial amendments will be notified to the IRB that gave a favourable opinion. Non-substantial amendments will not be notified to the accredited IRB and the competent authority, but will be recorded and filed by the sponsor.

### Safety report

#### Temporary halt for reasons of subject safety

In accordance to section 10, subsection 4, of the Dutch law of scientific research involving human subject (WMO), the sponsor will suspend the study if there is sufficient ground that continuation of the study will jeopardise subject health or safety. The sponsor will notify the accredited IRB without undue delay of a temporary halt including the reason for such an action. The study will be suspended pending a further positive decision by the accredited IRB. The investigator will take care that all subjects are kept informed.

##### (Serious) adverse events

Adverse events (AEs):

Adverse events are defined as any undesirable experience occurring to a subject during the study, directly related to the experimental interventions. All adverse events reported spontaneously by the subject or observed by the investigator or his staff will be recorded.Serious adverse events (SAEs):

A serious adverse event is any untoward medical occurrence or effect thatresults in death;is life threatening (at the time of the event);requires hospitalisation or prolongation of existing inpatients’ hospitalisation;results in persistent or significant disability or incapacity;is a congenital anomaly or birth defect; orany other important medical event that did not result in any of the outcomes listed above due to medical or surgical intervention but could have been based upon appropriate judgement by the investigator.

An elective hospital admission will not be considered as a serious adverse event.

SAEs that result in death or are life threatening will be reported expedited through the webportal *Toetsingonline* to the accredited IRB that approved the protocol. The expedited reporting will occur not later than 7 days after the responsible investigator has first knowledge of the adverse reaction. This is for a preliminary report with another 8 days for completion of the report. The sponsor will report the remaining SAEs twice a year in line listings.

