## Methods/Design

### Trial design

The PABLO study is a three-armed multicenter randomised controlled trial (RCT). The participants will be recruited from a specialized cancer hospital: the Netherlands Cancer Institute (NKI), Amsterdam, and a large teaching hospital: Rijnstate, Arnhem.

Participants will be randomised to one of the three study arms. Participants allocated to the first intervention arm will receive 6-month access to the intervention (IPAS). The second intervention arm will receive 6-month access to IPAS, as well as additional support by a monthly phone call with a physiotherapist (IPAS+TS). The control group will receive usual care and a leaflet with PA guidelines. The total study duration per participant is 12 months. This protocol will follow the SPIRIT guidelines. Figure 1 contains the flowchart for the study.

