#### Usual care

The control group will receive usual care and a leaflet with current physical activity guidelines for cancer survivors [31]. Both intervention groups will have access to the same leaflet via IPAS. The leaflet explains the physical activity guidelines and provides information on how the intensity of moderate to vigorous PA can be monitored by Borg rating of perceived exertion, a “talk-test” (when it becomes more difficult to talk in whole sentences) and heartrate self-monitoring. Although they are not actively referred, participants are not prohibited from participating in a rehabilitation or exercise programs with a physiotherapist in primary care, if they so wish. At 6 months, questions about participation in such programs will be included in the questionnaire.

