##### Follow-up of adverse events

Exercise-related AEs will be followed until they have abated, or until a stable situation has been reached. Depending on the event, follow up may require additional tests or medical procedures as indicated, and/or referral to the general physician or a medical specialist. SAEs need to be reported till end of study within the Netherlands, as defined in the protocol.

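### The non-serious adverse event definition requires a direct relation to the experimental interventions, so usual-care participants cannot have one, and recording depends on staff contact that differs by arm

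*Protocol article*

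**What the plan says.** All references are to the Protocol article.

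- **Adverse event.** The (Serious) adverse events section defines it as "any undesirable experience occurring to a subject during the study, directly related to the experimental interventions".
- **Recording.** The same section adds: "All adverse events reported spontaneously by the subject or observed by the investigator or his staff will be recorded". That gives two routes, joined by an or.
- **Serious adverse event.** Still in that section: "A serious adverse event is any untoward medical occurrence or effect" that meets one of the listed seriousness criteria. Relatedness is not among the conditions.
- **Follow-up.** Follow-up of adverse events states: "Exercise-related AEs will be followed until they have abated, or until a stable situation has been reached".
- **Control arm.** Usual care states: "The control group will receive usual care and a leaflet with current physical activity guidelines for cancer survivors". The leaflet also explains how to monitor exercise intensity, and participants are free to join a rehabilitation or exercise program in primary care.
- **Contact by arm.** IPAS+TS receives "additional support by a monthly phone call with a physiotherapist" (Trial design), preceded by a 45-minute face-to-face intake (IPAS with telephone support). The Abstract describes IPAS alone as fully automated. Its monthly online questionnaire covers activity levels and motivation (Interventions, IPAS). No scheduled staff contact is described for controls; their follow-up assessments are at 6 and 12 months (Table 4).

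**The concern.** Whether an event happened and whether the intervention caused it are separate questions. The article merges them for non-serious events: an event not directly related to an experimental intervention is not an adverse event at all. An exercise injury in a control who follows the leaflet or attends a local program therefore falls outside the definition, while the same injury in an IPAS participant can fall inside it. An event held to be unrelated leaves no adverse event record from which that judgement could later be reviewed.

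The recording routes add a second asymmetry. Spontaneous report and staff observation both need an occasion for the participant and staff to meet or speak. IPAS+TS has such an occasion every month; the other two arms do not.

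At stake is how any non-serious event counts can be read. The program promotes largely unsupervised exercise, and the Discussion foresees adding it to standard care if it proves (cost-)effective. A reader who sees such counts by arm could take a gradient produced by definition and contact for a difference in risk.

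**Working it through.** The document gives no adverse event rate and no figure to reproduce. The check is mainly a comparison of its own statements.

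**Step 1: what each rule admits.** Take one exercise injury, serious or not, in each arm.

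| Rule | Control | IPAS | IPAS+TS |
|---|---|---|---|
| Adverse event (must be directly related to the experimental interventions) | Cannot qualify | Can qualify | Can qualify |
| Serious adverse event (no relatedness condition) | Qualifies if serious | Qualifies if serious | Qualifies if serious |
| Follow-up of exercise-related adverse events | Fits exercise-related, but is not an adverse event | Can qualify | Can qualify |

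Two inconsistencies follow. A serious adverse event need not be an adverse event as defined. And exercise-related is not the same set as directly related to the experimental interventions: the control injury meets the first and not the second.

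**Step 2: opportunity for recording.** In IPAS+TS the physiotherapist asks at each monthly call how exercise has gone and takes notes on a standardized form. In IPAS alone the contact is automated, and its questionnaire is described as covering activity and motivation. For controls no scheduled staff contact is described. Table 4 lists no injury or adverse event item for any arm. Unequal detection is an inference from these facts; the document does not state it.

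**Step 3: illustration on assumed values.** The number per arm follows from the document: 246 / 3 = 82. Everything else here is assumed: the same true risk r of an exercise-related event in every arm, such events counting as related in the two intervention arms, and capture proportions c that are higher in IPAS+TS. Expected recorded events = 82 × r × c.

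| r | True events per arm | c, IPAS+TS | c, other arms | Recorded IPAS+TS | Recorded IPAS | Recorded control, current definition | Recorded control, relatedness dropped |
|---|---|---|---|---|---|---|---|
| 5% | 4.1 | 80% | 30% | 3.3 | 1.2 | 0 | 1.2 |
| 10% | 8.2 | 60% | 40% | 4.9 | 3.3 | 0 | 3.3 |
| 20% | 16.4 | 80% | 40% | 13.1 | 6.6 | 0 | 6.6 |
| 30% | 24.6 | 90% | 30% | 22.1 | 7.4 | 0 | 7.4 |

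With equal true risk, the ratio of recorded events in IPAS+TS to IPAS is simply the ratio of the capture proportions, here from 60/40 = 1.5 to 90/30 = 3. The control zero does not depend on any assumed value.

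**The case against.** The strongest reply is that nothing the trial plans to conclude is biased by this. Safety is not among the aims, it is not an outcome in Table 4, and the Statistical analysis section plans no comparison of adverse events. The safety section is about reporting and follow-up. That stands: the point concerns how counts may be read if they are reported by arm, not a planned analysis.

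It is also fair that an article leaves event forms, prompts and causality procedures to the full protocol. So the lack of a systematic question here is not in itself a fault. This does not rescue the definition, which the article prints in full.

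Other sources cover all arms alike: health-care use through the iMCQ at 6 and 12 months, and disease status and additional treatment from medical records. An event that led to care is therefore not invisible in IPAS or control. But the article assigns the iMCQ to costing and does not name it as a source of adverse events.

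Several stronger readings are tempting and are not supported:

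- *Only spontaneously reported events count.* Staff observation is a second route, and both routes govern recording, not the definition.
- *Controls can have no adverse events of any kind.* The serious adverse event definition has no relatedness condition, so serious events can be recorded in controls.
- *Unblinded staff decide relatedness before anything is recorded.* The article says that participants and researchers are unblinded, but not who judges relatedness or when.
- *Recorded counts will rise with contact whatever the true risk.* Counts depend on both risk and capture.

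**Conclusion.** The point holds in a limited form. As printed, the definition makes a non-serious adverse event impossible in the usual-care arm, and it agrees neither with the serious adverse event definition beside it nor with the follow-up rule after it. This is a rule stated in the text, not a detail left out. Because recording relies on spontaneous report or staff observation, and scheduled contact differs by arm, it is also reasonable to infer that non-serious counts would partly track contact and that IPAS alone is more exposed to missed events than IPAS+TS.

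The only size fixed by the document is the control count of zero non-serious events. The gap between the two intervention arms cannot be derived from it; the illustrated ratios of 1.5 to 3 rest wholly on assumed capture proportions. A reader might infer that a planned safety comparison is invalid, but no such comparison is stated. Nor would complete capture make one informative if risk is low: at an assumed 5%, about 4 events per arm would be expected.

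**What to change.** - Define an adverse event as any undesirable experience during the study, whether or not related to an intervention, and record relatedness as a separate attribute. Use the same base definition for serious events and for the follow-up rule, so that the three passages agree.
- Add one identical injury or health-event item to the existing 6- and 12-month questionnaires in all three arms.
- Base any description of non-serious events by arm on that item. List events learned in physiotherapist calls separately, and do not present the description as a powered safety comparison.

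The cost is a small amendment and one extra item in two questionnaires already sent to every participant. More events, most of them unrelated, will have to be recorded. If the full protocol already collects events in this way, only the definition needs changing.

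### The SAE exemption covers every elective admission, including one booked during the trial for a condition that arose or worsened after randomisation

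*Protocol article*

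**What the plan says.** The rule is in the protocol article, Safety report, subsection (Serious) adverse events. One of the listed grounds for seriousness is that an occurrence "requires hospitalisation or prolongation of existing inpatients’ hospitalisation". Directly after the list comes the exemption: "An elective hospital admission will not be considered as a serious adverse event".

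Three other statements determine what the exemption does in practice:

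- The same subsection defines an adverse event as "any undesirable experience occurring to a subject during the study, directly related to the experimental interventions". It is recorded when the participant mentions it or when study staff observe it.
- Only SAEs that are fatal or life threatening are expedited. For the rest, "The sponsor will report the remaining SAEs twice a year in line listings".
- The subsection Follow-up of adverse events says "Exercise-related AEs will be followed until they have abated, or until a stable situation has been reached", and foresees further procedures or referral to a specialist.

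**The concern.** The exemption turns on how an admission was scheduled. An exemption of this kind normally serves to keep out hospital stays that would have happened anyway, and for that purpose what matters is when the admission was planned and whether the condition was already there and stable. In this population, planned care after primary treatment is to be expected: the clinical data list includes "type of surgery, possible breast reconstruction, radiotherapy, chemotherapy, endocrine treatments". Exempting a procedure already scheduled at entry is reasonable.

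The sentence goes further than that. It also takes in an admission arranged after randomisation for something that began or got worse during the trial, including something attributable to the exercise. What is at stake is whether the SAE listings sent to the review board are complete, and whether serious events are counted on the same basis in the three arms.

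**Working it through.** No arithmetic applies: the point concerns a definition, and the article states no admission rate. The check was to look for any wording that narrows the exemption, and then to apply the rules to the kinds of admission that can occur.

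**Search for a limit.** The Safety report section and the rest of the article were read for any restriction by date of planning, by pre-existing or stable condition, or by relation to the intervention. There is none. The follow-up subsection closes by deferring to the protocol, but that phrase concerns how long SAEs are reported, not which admissions count.

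**Applying the text to cases.**

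1. *Admission planned before randomisation, such as a reconstruction already scheduled.* Exempt. This is a sensible result.
2. *Unplanned admission for a new event.* The hospitalisation criterion applies and the exemption is not engaged. The event is an SAE.
3. *Exercise-related injury treated by a scheduled admission booked during the trial.* It meets the hospitalisation criterion ("requires hospitalisation or prolongation of existing" inpatient care), and the exemption then removes it on that ground. If reported or observed, it is recorded and followed as an adverse event. Unless another criterion makes it serious, it does not enter the line listings.
4. *Condition that arose or worsened after randomisation, not judged directly related to the intervention, treated by a scheduled admission.* It falls outside the adverse event definition, which requires a direct relation. It is not an SAE on the hospitalisation ground either. Unless another criterion applies, neither safety definition captures it. Recurrence or progression is an exception in part: the section on socio-demographic and clinical data collects it from medical records, though not as a safety event.
5. *Fatal or life-threatening event.* Serious on its own ground and expedited as before.

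The exemption therefore does harm in cases 3 and 4 only.

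**Comparison of arms.** Control participants receive no experimental intervention, so the adverse event definition can hardly apply to them. The SAE definition carries no such condition and is the one that works alike in all arms. An over-broad exception to it therefore weakens the only safety count that can be compared between arms.

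**The case against.** The strongest reply is that this is a condensed article, that the authors probably meant pre-planned admissions, and that the full protocol may say so. That may be true of the intent. But the article does not merely leave a detail out. It states a rule, and the rule as stated is too broad.

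Other objections limit the point, and they stand:

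- *A reader might infer that the exemption contradicts the hospitalisation criterion.* It does not. The text gives a general rule followed by an exception, and a scheduled admission can be read as not in itself an untoward occurrence. The defect is the width of the exception.
- *A reader might infer that serious exercise harm disappears from the safety data.* The documents do not support that. Death, threat to life and lasting disability remain as grounds for seriousness. So does the important-medical-event ground, although it rests on investigator judgement and is worded for events in which treatment averted the listed outcomes, so it may not fit an event that did lead to admission. A related injury that is reported or observed is still recorded and followed.
- *A reader might infer that the exemption falls mainly on the harm most likely from this intervention, because exercise injuries tend to be treated by planned admission.* Nothing in the documents says so.
- *A reader might try to count the lost SAEs by applying an assumed percentage to the program participants.* The documents offer no basis for a percentage. A rate of all planned admissions for new or worsened conditions would also mix unrelated events with intervention-related ones, and it would leave out the control arm, to which the exemption applies equally.
- *A reader might infer that a stated conclusion of the trial rests on the SAE count.* The Discussion makes adoption conditional on (cost-)effectiveness, Table 4 lists no safety outcome, and the Statistical analysis section describes no SAE comparison.

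**Conclusion.** The point holds as a wording defect in a safety definition. Followed literally, the article leaves out of the twice-yearly SAE listings any event whose only ground for seriousness is hospitalisation and whose admission was scheduled during the trial, even if the condition is new or has worsened since randomisation. The number of such events is unknown and probably small. Expedited reporting, the sample size and the primary analysis are untouched.

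The conclusion rests on reading the sentence as it stands and on no qualifying text existing in the article. If the full protocol already limits the exemption, the article's sentence needs only to be aligned with it.

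**What to change.** Limit the exemption to elective admissions that were planned before randomisation, or that are for a pre-existing condition that has not worsened since randomisation. State that every other admission is assessed under the hospitalisation criterion, in all three arms. The SAE form should record when the admission was planned and whether the condition was present and unchanged at randomisation.

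This takes one sentence in the safety section and a line on the form. The downside is a slightly higher SAE count and a few more line-listing entries. Only the definition of a reportable event changes; clinical management does not.
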